### Objectives

#### Primary objective

To determine the prevalence and risk factors of GI intolerance and symptoms in patients: with kidney failure (dialysis only); before transplant (candidate listed on the transplant waiting list or have a pre-emptive donor); and after kidney transplantation.

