#### Longitudinal cohort study

Recruitment of participants will occur anytime pre-transplant and the following will be collected (Table 1):General patient contact information, demographic characteristics, medical history, and CKD health status via the Observational Questionnaire (Baseline).The baseline assessments, pre-transplant of observational data via the Observational Questionnaire (Baseline) which will collect transplant status, current medications and supplements, general health via the EQ-5D Questionnaire [17], faecal characteristics using the Bristol Stool Chart [18], gastrointestinal symptoms via the Gastrointestinal Symptom Rating Scale (GSRS) [19, 20], quality of life using the Gastrointestinal Quality of Life Scale (GIQLS) [21], personal management strategies of gut health and GI symptoms, dietary patterns using the Food Frequency Questionnaire [22], and safety parameters and adverse events.To repeat the instruments, the Observational Questionnaire (Follow-Up) will be administered at 4-, 12-, and 28-weeks post-transplant (28 weeks being the final follow-up time-points). This questionnaire contains the same instruments without the patient contact information and demographic sections.

**Table 1 Tab1:** Study Visit Schedule

Task	Time points				
	Visit 1		Visit 2	Visit 3	Visit 4
	Recruitment and baseline (anytime pre-Tx)	Tx	4 wk. post-Tx	12 wk. post-Tx	28 wk. post-Tx
**Screening** against eligibility criteria	✓				
**Participant Information Consent Form:** Combined form for all 3 study arms	✓				
**Questionnaire (baseline)**	✓				
**Questionnaire (follow-up)**			✓	✓	✓
**Qualitative Interview**	✓				✓
**Discrete Choice Experiment Survey**				✓	
**Tx:** transplant; **wk:** weeks.					

The primary outcomes are: (1) prevalence of GI intolerance (any severity) in patients with kidney failure and kidney transplants; and (2) change in GI symptom burden before and after transplantation. Secondary outcomes are: (1) risk factors of GI intolerance; (2) stool characteristics; (3) general health status, and (4) quality of life.

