Instruments: the observational questionnaires (baseline and follow-up) will collect a broad range of both clinically important and patient-reported outcomes [23] using a variety of validated instruments. The EQ-5D tool is a 5-question Likert scale for measuring general health status according to activities of daily living [17]. The Bristol Stool Chart is a 7-point illustrative scale for identifying different categories of stool characteristics [18]. The GSRS instrument comprises of 15 items combined into five symptom-domains of reflux, abdominal pain, indigestion, diarrhoea and constipation. The GSRS is a graded scale, with a score of 1 representing the absence of any GI symptoms, whereas a score of 7 representing severe GI symptoms [19–21]. The Food Frequency Questionnaire is a validated 131-item dietary assessment tool to capture a patient’s content, frequency, and portion sizes of food and beverages over a specified time period, ranging from 1 to 12 months depending on the question [22].

Statistical analysis: we will undertake a descriptive analysis of the prevalence and management strategies of GI intolerance in patients with kidney failure and have a kidney transplant. Baseline characteristics and dietary patterns will be compared between recipients with and without GI intolerance using chi-square (to compare categorical variables), analysis of variance (compare means for normally distributed variables) and Kruskal-Wallis tests (to compare medians for non-normally distributed variables). Longitudinal mixed models with random intercepts will be conducted to assess the relationship between dietary patterns and GI intolerance, accounting for confounders including age, sex, medication use, and CKD stage.

*Sample size calculation*: If the true prevalence of GI intolerance and symptoms is 7–10% in patients with kidney failure, a sample size of 100 will ensure 95% certainty that the prevalence measure in this sample between 5 to 15%, where n = minimum sample, p = estimated prevalence, q = 100-p, E = 5 (margin of sampling error) $$n= pq/{\left(\frac{E}{1.96}\right)}^2$$ [24].

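### The sample size paragraph promises 95% certainty that n = 100 does not deliver across 7–10%, and it sizes one pooled group while the primary objective names three populations

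*Protocol article*

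**What the plan says.** The calculation is in the protocol article, Longitudinal cohort study, under the sample size heading. It starts from one prevalence in one population: "If the true prevalence of GI intolerance and symptoms is 7–10% in patients with kidney failure". It then states that "a sample size of 100 will ensure 95% certainty that the prevalence measure in this sample between 5 to 15" per cent. The formula is n = pq/(E/1.96)², "where n = minimum sample, p = estimated prevalence, q = 100-p", and "E = 5 (margin of sampling error". The text gives no number per group and no split of the 100.

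The primary objective covers more than one population: "To determine the prevalence and risk factors of GI intolerance and symptoms in patients: with kidney failure (dialysis only); before transplant", the last of these meaning "candidate listed on the transplant waiting list or have a pre-emptive donor); and after kidney transplantation". The first primary outcome is the "prevalence of GI intolerance (any severity) in patients with kidney failure and kidney transplants". The eligibility criteria list dialysis-only patients separately from waitlisted and pre-emptive candidates. The cohort is recruited before transplant and followed at 4, 12 and 28 weeks after it.

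**The concern.** There are two mismatches. First, the printed range of 5 to 15% is 10 ± 5, but the sample size of 100 is what the formula gives at 7%. The paragraph takes its range from one end of the planning interval and its sample size from the other. Second, prevalence is the primary result and is wanted for three populations, but only one precision calculation is given, for a pooled kidney-failure group, and none for recipients.

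Prevalence in these patients is meant to define the burden of GI intolerance and inform the design of later intervention trials. A reader who carries ±5 points over to each population would plan on estimates that are firmer than the cohort can supply.

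**Working it through.** **Inputs from the documents.** Sample size paragraph: p = 7 to 10 (per cent), E = 5, multiplier 1.96, n = 100, target range 5 to 15%. Background: GI intolerance in up to 80% of dialysis patients, and GI side effects of immunosuppression in up to 50% of transplant recipients.

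**Step 1. Reproduce the plan's figure.** With (5/1.96)² = 6.508:
- p = 7: 7 × 93 / 6.508 = 100.04, which reproduces 100
- p = 8: 8 × 92 / 6.508 = 113.1
- p = 9: 9 × 91 / 6.508 = 125.9
- p = 10: 10 × 90 / 6.508 = 138.3, so 139

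The figure of 100 matches only the lowest planning value.

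**Step 2. Margin at n = 100.** Half-width = 1.96 × √(p(100 − p)/n):
- p = 7: 1.96 × √6.51 = 5.00 points, giving 2.0 to 12.0%
- p = 10: 1.96 × √9.00 = 5.88 points, giving 4.1 to 15.9%

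Neither interval lies inside 5 to 15%.

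**Step 3. The certainty statement as worded.** Taken literally, it is the chance that a sample of 100 contains 5 to 15 affected people. The exact binomial sum over x = 5 to 15 is:
- true prevalence 7%: 0.835
- true prevalence 8.5%: 0.924
- true prevalence 10%: 0.936

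All three are below 0.95. The shortfall is largest at 7%, because the lower limit of 5% is then only 2 points away. Reading the statement as a confidence interval does not help. The Wilson 95% interval is 3.4 to 13.7% for 7 of 100 and 5.5 to 17.4% for 10 of 100.

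**Step 4. The populations in the primary objective.** Suppose 100 is the cohort total and contains both dialysis-only patients and candidates. Each baseline group is then smaller than 100. Recipients come from candidates who are transplanted and still followed, so they cannot outnumber the candidates. At 7%, 100 people only just reach ±5, and any smaller group misses it. At prevalences above 7% and up to 10% the margin is wider still. This conclusion needs no particular split; its size does.

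Half-widths in points (70 and 50 are assumed group sizes, because the document gives none):

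| n | p = 7% | p = 10% |
|---|---|---|
| 100 | 5.00 | 5.88 |
| 70 | 5.98 | 7.03 |
| 50 | 7.07 | 8.32 |

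Relative to ±5, a group of 50 is 7.07/5 = 1.4 to 8.32/5 = 1.7 times as wide.

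**Step 5. Sensitivity to the Background figures.** At n = 100, a prevalence of 50% gives 1.96 × √25 = 9.8 points and 80% gives 1.96 × √16 = 7.8 points.

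**The case against.** The best defence is that the paragraph limits itself to patients with kidney failure and to the sample as a whole. It nowhere promises ±5 points for recipients or for a subgroup. The first primary outcome can be read as two populations, the first being the pooled baseline cohort, and for that cohort the formula does give ±5.00 at 7%. The number is called a minimum, so more than 100 could be enrolled. The study is descriptive, no test rests on this figure, and achieved intervals will be reported from the data. All of this stands. It makes the point a should-fix matter and not a fatal one, but it does not rescue the 95% statement, which fails for the pooled 100 before any split.

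Three stronger readings are tempting, and the documents do not support them.
- **Intervals two to four times wider than stated.** At the planning prevalence, a group of 50 is 1.4 to 1.7 times as wide. A ratio near four needs the Background prevalences together with about 20 people: 1.96 × √(2500/20) = 21.9 points, or 4.4 times. Both Background figures are upper limits, and the 50% concerns side effects of immunosuppression, not GI intolerance of any severity.
- **The 100 divided equally into three groups of about 33.** Recipients are a subset of the candidates, so before- and after-transplant estimates come from the same people. The baseline division is two-way, with later loss.
- **None of the three estimates can come near ±5 under any circumstances.** That each falls short depends on 100 being the total and both baseline groups being present. If nearly all were candidates and were transplanted, those two estimates would approach ±5 at 7%, and the dialysis-only estimate would be very imprecise.

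**Conclusion.** The precision statement is wrong as written and should be corrected. For the pooled 100, no assumption about group sizes is needed: the margin is ±5.0 points at 7% and ±5.9 at 10%, the formula asks for 139 at 10%, and the chance of a sample prevalence in 5–15% is 84% or 94%, not 95%.

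The calculation also does not cover the populations in the primary objective. If 100 is the cohort total and both baseline groups are represented, each of the three estimates is less precise than ±5 throughout 7–10%. How much less cannot be fixed from the document, which gives neither a split nor the proportion expected to be transplanted and followed. Groups of 50 to 70 would have margins between about ±6.0 and ±8.3 points.

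**What to change.** Keep n = 100 and revise the one paragraph:
- Delete the statement of 95% certainty for 5 to 15%.
- State that 100 people give a 95% half-width of about ±5.0 to ±5.9 points at a prevalence of 7–10%, rising to as much as ±9.8 points if prevalence is nearer the upper figures of 50–80% in the Background.
- State that this precision applies to the pooled baseline sample only.
- Give the expected number and 95% half-width for dialysis-only patients, candidates and post-transplant recipients, at a named planning prevalence.

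The cost is a reworded paragraph and a short table, with no extra patients or procedures. The downside is that the stated precision becomes less favourable.

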#### Semi-structured interview study

##### Participant recruitment and selection

Participants who were identified as eligible for the observational longitudinal study at recruitment (anytime pre-transplant), and who reported the presence of GI symptoms, burden and intolerance, will be invited to participate in the qualitative semi-structured interviews. This will be a longitudinal qualitative study and purposive sampling will be used to ensure a broad range of demographics are included in this study. We plan to enrol a minimum of 30 CKD patients from this study population until saturation. Participants will be interviewed twice: once at baseline (anytime pre-transplant) (Visit 1, Table 1) and once post-transplant at the 28-week follow-up (Visit 4, Table 1).

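### At the planning prevalence of 7–10%, a cohort of 100 yields about 7–10 symptomatic patients against a minimum of 30 interviewees; prevalence, cohort precision and interview target need to be reconciled

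*Protocol article*

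**What the plan says.** Four parts of the protocol article bear on this point.

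- **Longitudinal cohort study, sample size calculation.** The cohort is sized on this premise: "If the true prevalence of GI intolerance and symptoms is 7–10% in patients with kidney failure, a sample size of 100". The formula's terms are given as "where n = minimum sample, p = estimated prevalence, q = 100-p, E = 5 (margin of sampling error").
- **Eligibility criteria.** Patients enter the cohort whether or not they have, or have had, GI symptoms.
- **Semi-structured interview study, participant recruitment and selection.** The pool is "Participants who were identified as eligible for the observational longitudinal study at recruitment (anytime pre-transplant"), narrowed to those "who reported the presence of GI symptoms, burden and intolerance, will be invited to participate in the qualitative semi-structured interviews". The target is: "We plan to enrol a minimum of 30 CKD patients from this study population until saturation". Sampling is purposive, and each person is interviewed before transplant and again at week 28 after it.
- **Background, and the primary outcomes in the cohort section.** The Background puts GI intolerance in dialysis patients at as much as 80%. The first primary outcome counts intolerance of any severity.

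**The concern.** The cohort calculation and the interview target rest on figures that do not fit together. If recruitment ignores symptoms, the symptomatic share of the cohort should be close to the prevalence. At 7–10% of 100, that is far fewer people than the interview minimum, before allowing for refusals, for purposive selection, or for patients who do not reach the week-28 interview.

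The interviews are the route to the secondary objective. The first interview is also meant to inform the attributes of the discrete choice survey, so a shortfall would carry into the third study. The survey may also recruit post-transplant patients from the renal clinics; the interview section names no such additional source.

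**Working it through.** **Inputs.** Prevalence 7–10%, n = 100, E = 5 points and z = 1.96 (sample size calculation); at least 30 symptomatic interviewees (interview study); recruitment irrespective of symptoms (Eligibility criteria); up to 80% in dialysis patients (Background).

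**1. The plan's own figure.** n = p(100 − p)/(5/1.96)², where (5/1.96)² = 6.508.
- p = 7: 651/6.508 = 100.04, which matches the stated 100.
- p = 10: 900/6.508 = 138.3, so 139.

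The stated 100 therefore corresponds to the lower end of the planning range only.

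**2. Symptomatic patients at the planning prevalence.** Expected number = N × p.
- N = 100: 7 at 7%, 10 at 10%. The shortfall against 30 is 20–23.
- Exact binomial chance of at least 30 among 100: 5 × 10⁻¹² at 7%, 2.4 × 10⁻⁸ at 10%.
- N = 139 (the formula's answer at 10%): 13.9 expected at 10%, and the chance of at least 30 is 4 × 10⁻⁵.

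**3. Patients needed to supply 30, if all agree.**
- To expect 30: 30/0.10 = 300 and 30/0.07 = 429.
- For a 90% chance of at least 30: 368 at 10% and 528 at 7%.

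**4. Prevalence needed for 100 patients to supply 30.** Required prevalence = 30/(100 × uptake). The plan gives no uptake rate, so the rates below are assumptions.

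| Uptake | Prevalence needed to expect 30 |
|---|---|
| 100% | 30% |
| 70% | 43% |
| 50% | 60% |

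Even at 30% prevalence with full uptake, the chance of reaching 30 is only 0.54. At 50% or 80% prevalence with full uptake it exceeds 0.9999.

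**5. What a higher prevalence does to the cohort's precision.** Margin with n = 100 is 1.96 × √(p(1 − p)/100).

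| Prevalence | Margin at n = 100 | n by the plan's formula for ±5 points |
|---|---|---|
| 30% | 1.96 × 0.0458 = ±9.0 points | 2100/6.508 = 322.7, so 323 |
| 50% | 1.96 × 0.0500 = ±9.8 points | 2500/6.508 = 384.2, so 385 |
| 80% | 1.96 × 0.0400 = ±7.8 points | 1600/6.508 = 245.9, so 246 |

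The product p(100 − p) equals 651 at both p = 7 and p = 93 and is larger everywhere between. Above 7%, no prevalence up to the Background's 80% gives a margin of 5 points with 100 patients. None at or near 7% supplies 30 symptomatic patients from 100.

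**The case against.** A reader might infer that the interview target cannot be met as written. The document does not support that, for three reasons.

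- The pool is patients identified as eligible for the cohort, not the 100 enrolled, and the formula calls n a minimum. Neither section caps the pool at 100.
- The 7–10 is an expected count, not a fixed one.
- The Background's figure of up to 80% in dialysis patients would make 30 from 100 easy. With an outcome of any severity and many dialysis patients in the cohort, the weak number may be the 7–10% rather than the 30.

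All three points stand, and they limit the finding, but they do not remove it. No larger cohort or screening number is given. Table 1 puts both interviews at cohort visits under one combined consent form, and the target is drawn from this study population, so the interviews appear to be nested in the cohort. The 80% is an upper figure for dialysis patients, not an estimate for this cohort. Adopting a high prevalence resolves the interview count at the expense of the stated precision (step 5).

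Nor is the symptom criterion in itself a mistake. It fits an interview about the causes, impact and management of symptoms, and relaxing it is a design trade-off.

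**Conclusion.** The inconsistency is real, but it is one of mutually incompatible figures and not proof that the interviews are unachievable. On the planning prevalence, 100 unselected patients give about 7–10 symptomatic patients against a minimum of 30, and about 300–429 would have to be screened to expect 30. On a prevalence high enough to supply 30 from 100, the cohort gives roughly ±8 to ±10 points at the values tabulated, instead of ±5.

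This rests on two readings: that interviews are nested in a cohort of about 100, and that the prevalence used for sizing and the symptom criterion for interview describe broadly the same condition, as their similar wording suggests. It assumes full uptake; refusals and loss before week 28 would enlarge the shortfall, but the plan gives no rates for them. Which of the three numbers is wrong cannot be settled from the document.

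**What to change.** 1. Reconcile the Background, the sample size calculation and the interview recruitment section on one justified prevalence for pre-transplant GI symptoms of any severity. If the 7–10% refers to a narrower definition, say so.
2. Restate the precision that n = 100 delivers at that prevalence, or change n if ±5 points is to be kept.
3. In the interview section, replace the unsupported minimum of 30 with the number of symptomatic interviewees expected from 100, or state how many eligible patients will be approached to reach 30, with the assumed uptake.

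If the reconciled prevalence stays low, one option is to sample interviewees purposively across the whole cohort, stratified by baseline GSRS status, which is already collected. The drawback is that most interviewees would then have few pre-transplant symptoms to report, so the number of symptomatic accounts would not rise. Adding post-transplant clinic patients, as the survey does, would not fill the gap in the present design, because they cannot give the pre-transplant interview.

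The restatement costs a few sentences and probably a minor ethics amendment, with no extra patients or visits. Extra recruitment or screening arises only if the sponsor chooses to keep ±5 points at a higher prevalence, or to keep 30 symptomatic interviewees at a low one.

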##### Data collection

A semi-structured interview will be conducted with each participant in their choice of setting either in a clinic room or via video conference. The interviews will be administered by the study research coordinators who are research academics with training in qualitative research. Some participants may be known to the interviewer but only from the recruitment process. The interviewers will not have clinically treated the participants.

The interview guide will include the following sections: (1) demographics; (2) Interview 1: general perspectives and experience of gut health in CKD; perceived causes, impact and management of GI symptoms in CKD (this includes both self-management and medically advised); expectations of transplantation; reasons for participating in the study; (3) Interview 2: experience of being in the study; experience of the transplant; experience of GI symptoms post-transplant.

The guide was developed following a review of the literature and discussion among the research team consisting of multidisciplinary clinicians and researchers and a consumer advisor [25–32].

##### Data analysis

Thematic analysis: interviews will be recorded with the participant consent and transcribed verbatim. Transcripts and field notes will be thematically analysed to independently code all transcripts and notes line by line by two study personnel to identify concepts.

#### Discrete choice experiment

All participants identified as eligible for the observational longitudinal study, as well as post-transplant patients presenting at the renal clinics, will be invited to participate in the discrete choice experiment. We plan to enrol 70 participants and the survey will be administered at either Visit 3 or Visit 4 (Table 1), or anytime within 4 months post-transplant. Participants will be administered the electronic survey directly after attending their usual medical appointment with their surgeon using a clinic computer or tablet.

Figure 2 provides an example question of the attributes and levels. Participants will be identified by their participant study identification number which will be linked to their demographic information. The survey will be administered as follows: (1) instructions and introduction of the study aim, (2) explanation of attributes, (3) explanation of choice sets. In the survey, participants will be given 5 to 10 choice sets to answer their most preferred scenario of post-transplant treatment options. The results of the first qualitative interview (Study 2) will inform the attributes for this survey. However, the anticipated attributes are: mode of taking supplements; average cost per month; dietary changes; and post-transplant prescribed immunosuppressive medications. The survey was developed following a review of the literature and discussion among the research team consisting of nephrologists and public health (qualitative) academics [33–36].

**Fig. 2 Fig2:**
[figure not shown]
Example of Discrete Choice Analysis questions

Statistical Analyses: we will use NLOGIT, version 5.0 [37] to analyse the data. To best the extent to which results were consistent with the researchers’ prior expectations, internal validity will be assessed by examining the signs and significance of parameter estimates [38].

